### Efficacy Outcome

The primary outcome is the treatment success rate, defined as the absence of the pathogen, as indicated through the NAAT. We set the superiority margin at 10%. The secondary outcomes include the change in bacterial load from pre- to posttreatment and the emergence of posttreatment nucleotide polymorphisms in mutant strains compared with those in pretreatment samples. The bacterial load will be measured as previously reported [28]. For the primary outcome in the FAS, with or without the G248T (S83I) mutation, rates and their 95% CIs will be computed. The chi-square test will be used to assess the statistical significance of treatment success between groups. This primary analysis will also be conducted for participants with the G248T mutation in the per-protocol set. In terms of secondary endpoints, differences, and rates of change in the bacterial load will be analyzed using either the 2-tailed Student *t* test or the Mann-Whitney *U* test. The rate and 95% CI of posttreatment resistance mutations in the FAS group will also be estimated using the positive cure confirmation results.

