**Methods:**

We will conduct this randomized controlled trial at multiple centers in Japan. Eligible participants include adults aged 18 years or older with a confirmed *M*
*genitalium* infection, as determined through the nucleic acid amplification test. Patients will be randomly assigned using a stratified approach based on the treatment facility and infection site. The interventions comprise oral sitafloxacin (200 mg) daily for 7 days (with optional pretreatment of oral doxycycline, 200 mg, daily for up to 7 days), with a control group receiving oral doxycycline (200 mg) daily for 7 days followed by moxifloxacin (400 mg) daily for another 7 days. The primary outcome is the treatment success rate with a superiority margin of 10%, as confirmed through the nucleic acid amplification test. Secondary outcomes encompass changes in the bacterial load at the urogenital or rectal sites and the emergence of posttreatment-resistant mutant strains.

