### Statistical Analysis

The sample size has been determined based on previous treatment success rates and specific assumptions. In a preliminary study, we determined that sitafloxacin achieved a treatment success rate of 92.9% against *M genitalium* with the *parC* G248T (S83I) mutation, in conjunction with wild-type *gyrA* [20]. Furthermore, sitafloxacin demonstrated a 78.9% success rate against strains carrying the *parC* G248T (S83I) mutation based on our preliminary data, and Murray et al [27] reported a moxifloxacin success rate of 41.2% against such strains. Accordingly, the success rates of sitafloxacin and moxifloxacin were anticipated to be 80% and 42%, respectively. With a 5% significance level (2-sided) and 80% statistical power for precise analysis, we aimed to enroll 50 participants per group (totaling 100 cases), considering the prevalence of the G248T mutation. Additionally, an expected dropout rate of approximately 10% was factored in, leading to a calculated sample size of 112 participants, evenly distributed across treatment groups, to robustly assess the efficacy of sitafloxacin and moxifloxacin against specific mutations in *M genitalium*.

Primary analyses regarding efficacy primarily rely on the full analysis set (FAS), which encompasses all registered participants, excluding ineligible participants and those not receiving the study drugs. To evaluate sensitivity, the analysis will be conducted for the per-protocol set, which consists of the study population, excluding cases of major protocol violations and discontinuations from the FAS. To evaluate safety, the analysis will be conducted for the safety analysis set, which includes all registered participants except those not receiving the study drug. Baseline characteristics of the study participants, both discrete and continuous, will be summarized. Discrete data will be presented as frequencies and percentages, whereas continuous data will be presented as descriptive statistics such as the mean and SD. Data will be analyzed with STATA (version 16.0; StataCorp), SAS software (version 9.4; SAS Institute), and R (version 4.1.2; R Foundation for Statistical Computing); the sample size calculation was done using Power Analysis and Sample Size 2022 (NCSS Statistical Software).

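### The plan sets a 10% superiority margin but tests the primary outcome with an ordinary chi-square test of no difference, so a significant result would not show that the margin was met

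*Protocol article*

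**What the plan says.** The abstract (Methods) attaches the margin directly to the primary outcome: "The primary outcome is the treatment success rate with a superiority margin of 10" percent. The Efficacy Outcome section repeats it: "We set the superiority margin at 10" percent. The same paragraph names the test: "The chi-square test will be used to assess the statistical significance of treatment success between groups". For estimation it says that "rates and their 95% CIs will be computed".

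The Statistical Analysis section sizes the trial "With a 5% significance level (2-sided) and 80% statistical power for precise analysis", with planning rates given as "the success rates of sitafloxacin and moxifloxacin were anticipated to be 80% and 42%, respectively", and arrives at 50 per group before dropout. The margin is not mentioned there. The article states no shifted null hypothesis, no interval for the difference between groups, and no rule comparing a confidence limit with 10 points.

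**The concern.** Superiority with a margin of 10 points means rejecting H0: p(sitafloxacin) − p(moxifloxacin) ≤ 0.10. An ordinary two-group chi-square test addresses H0: p(sitafloxacin) − p(moxifloxacin) = 0. The article therefore gives a criterion and a test that answer different questions, in the same paragraph.

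If a significant chi-square result is read as meeting the criterion, the trial could report superiority by 10 points on data that do not exclude a benefit close to zero. If instead the margin is applied after the results are seen, the hurdle for success changes after the fact. In an open-label trial that is already enrolling, the decision rule should not be open to either reading.

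**Working it through.** **Inputs.** Margin 10 points (abstract; Efficacy Outcome), read as a risk difference because no scale is given. Two-sided 5% level, that is 2.5% one-sided against a margin. Power 80%, planning rates 80% and 42%, 50 per group (Statistical Analysis). Allocation 1:1 (Randomization and Blinding).

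**1. The plan's own sample size.** The dropout step reproduces: 50/0.9 = 55.6, so 56 per group and 112 in total. The origin of 50 cannot be settled:

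- Zero-difference chi-square: n = [1.96·√(2·0.61·0.39) + 0.842·√(0.80·0.20 + 0.42·0.58)]² / 0.38² = 24.6, so 25 per group (30 with continuity correction).
- Margin of 10 points, unpooled: n = (1.96 + 0.842)²·(0.1600 + 0.2436) / (0.38 − 0.10)² = 40.4, so 41. Farrington–Manning gives 45. With continuity correction these become 48 and 52.
- 25/0.5 = 50 also fits if G248T prevalence is assumed to be 50%. The article mentions prevalence in this calculation but gives no figure for it.

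So 50 does not show whether the margin was used in the sizing.

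**2. How often the chi-square test is significant when the margin is only just reached.** All pairs of binomial counts were enumerated with a true difference of exactly 10 points. The table gives the probability of a significant result in favour of sitafloxacin with 50 per group.

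| Moxifloxacin / sitafloxacin | Chi-square | Farrington–Manning test of 10 points |
|---|---|---|
| 42% / 52% | 18.3% | 2.7% |
| 60% / 70% | 17.9% | 2.4% |
| 70% / 80% | 21.1% | 2.4% |
| 80% / 90% | 30.2% | 2.7% |

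With 56 per group the chi-square figures run from 18% to 32%.

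**3. Example.** Take 40/50 against 30/50. The difference is 0.20 and the pooled rate 0.70, so z = 0.20/√(0.7·0.3·2/50) = 2.18 and p = 0.03. The Wald 95% interval is 0.20 ± 1.96·√(0.8·0.2/50 + 0.6·0.4/50) = 2.5 to 37.5 points; the score lower limit is about 2 points. Against 30/50, the score lower limit is 8.9 points at 43/50 and first passes 10 at 44/50 (11.2). Against 21/50, the chi-square test is significant from 31/50, but the margin is met only from 36/50.

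**4. Power under each hypothesis, 50 per group.** At 80% v 42%, power is 98% for the chi-square test and about 84% for the score test of the margin. Those planning rates are for G248T strains, whereas the primary analysis is in the full analysis set, which also contains other strains. As an assumption only, treat the 68.3% of strains with any *parC* mutation (Introduction) as G248T, and take wild-type success as 100% for sitafloxacin and 96.5% for moxifloxacin (Introduction). Then:

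- sitafloxacin: 0.683·0.80 + 0.317·1.00 = 0.863
- moxifloxacin: 0.683·0.42 + 0.317·0.965 = 0.593

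Power is then about 88% for the chi-square test but about 50% for the margin, and about 97 per group would be needed for 80% power against the margin. At assumed prevalences of 50% to 80%, power against the margin runs from about 28% to 67% (unpooled approximation).

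**The case against.** The article never says that p < 0.05 establishes a 10-point benefit. Its Discussion and Conclusions speak only of superior efficacy, and for that claim a two-sided 5% chi-square test is valid. On this reading the margin may be a loose term for a minimum relevant difference, and the 18–30% is power at a 10-point benefit, not an error rate. A full protocol or SAP, not shown, may also contain the margin rule; some margin-based calculations do land near 50 per group. The 30% requires a moxifloxacin success rate of 80%, well above the planning rate of 42%. And adopting the margin as the primary hurdle has a real price in power.

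Much of this is fair, but it does not remove the contradiction. If simple superiority was meant, the test is right and the margin statement is wrong, so the text still needs correcting. The article is not silent on the test: it names a margin and a test that ignores it, so any margin rule held elsewhere would have to supplement or override the published wording. The 30% should be read with its 80% control rate; at control rates of 42–70% the range is 18–21%. The power point stands and belongs in the sponsor's decision.

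**Conclusion.** The concern holds and must be fixed, because it affects the primary decision rule. If the chi-square result is taken as evidence for the stated margin, the one-sided error rate for that claim is about 18–21% at moxifloxacin success rates of 42–70%, and 30% at 80%, against a nominal 2.5%. This assumes the margin is an absolute risk difference, 50 analysed per group, and that a significant chi-square result would be reported as meeting the margin. If the sponsor intended only simple superiority, the chi-square test is sound and the fault lies in the margin stated in the abstract and the Efficacy Outcome section.

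**What to change.** Make the primary analysis the two-sided 95% score interval (Miettinen–Nurminen or Farrington–Manning) for the risk difference in the full analysis set. Declare superiority by the margin only if the lower limit exceeds 10 points, and simple superiority if it exceeds 0. The two claims are nested and read from one interval, so no alpha is spent. At a difference of zero the Farrington–Manning score test is the Pearson chi-square test, so the simple-superiority claim loses nothing. State that the margin is on the risk-difference scale.

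If only simple superiority was intended, delete the margin from the abstract and the Efficacy Outcome section, or relabel it as a clinically relevant difference with no role in the decision.

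Either option is a change of protocol and SAP wording, with no new data, to be made before any comparison of the groups. The margin claim is harder to meet: power is about 84% at 80% v 42%, and about 50% at the assumed 86% v 59%. The sponsor should accept that openly or revisit the sample size if the margin claim is to be the primary one.

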## Introduction

The increase in the number of resistant strains of *Mycoplasma genitalium* is a global concern. The global prevalence of *M genitalium* in the general population ranges from 1.3% to 3.9% [1]. The prevalence of macrolide resistance-associated mutations (MRMs) has increased over the decades [2]. Furthermore, regional variations in resistant strains have been observed, with the prevalence of MRMs in the American and Western Pacific regions exceeding that in European countries [2]. The prevalence of quinolone resistance-associated mutations (QRAMs) has been increasing in the Western Pacific regions, including Australia, New Zealand, China, and Japan, making these regions focal points for resistance mutations [3-7]. The current national guidelines recommend resistance-guided sequential therapy for *M genitalium* infections when macrolide resistance testing is available; otherwise, empiric sequential therapy is recommended, commencing with doxycycline followed by fluoroquinolone [8-11]. For macrolide-susceptible strains, sequential therapy involves an initial cycle of doxycycline treatment followed by azithromycin, whereas for macrolide-resistant strains, it entails an initial cycle of doxycycline treatment followed by fluoroquinolone. According to Australian studies, resistance-guided therapy with doxycycline followed by azithromycin attains a high efficacy of 92% to 95.4% against macrolide-susceptible strains, whereas doxycycline followed by moxifloxacin achieves a high efficacy of 95.4% against macrolide-resistant strains, and doxycycline followed by sitafloxacin demonstrates a high efficacy of 95% against macrolide-resistant strains [12-14]. However, the cure rate of fluoroquinolone-based therapies depends on the prevalence of QRAMs, which include *parC* and *gyrA* mutations. Specifically, S83 and D87 mutations in *parC*, as well as M95, G93, and D99 mutations in *gyrA*, have been linked to treatment failure with moxifloxacin and sitafloxacin [15-19]. Additionally, combined *parC* and *gyrA* mutations limit the efficacy of fluoroquinolone-based therapy more significantly than single mutations [19,20]. As sitafloxacin, a newer-generation fluoroquinolone, is not widely available, direct comparisons between moxifloxacin and sitafloxacin treatments are lacking. Sitafloxacin exhibits higher efficacy against QRAM-resistant strains [14,17,18] and demonstrates a lower minimum inhibitory concentration relative to moxifloxacin in QRAM-resistant strains based on minimum inhibitory concentration assays [17,18]. Murray et al [14] conducted a clinical study and demonstrated that sitafloxacin-based sequential therapy for the most common *parC* G248T (S83I) mutant strains achieved a higher success rate than moxifloxacin-based sequential therapy. However, as previously mentioned, they did not directly compare the 2 drugs but instead retrospectively compared them at different times. Given the fluctuating numbers of mutant-resistant strains in recent years, a randomized clinical trial would be a more suitable approach to investigate the efficacy of these 2 drug regimens [14,21].

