
In Japan, the prevalence of resistant strains is high [3,21]. Ando et al [3] reported that 89.6% of strains harbored MRMs, with 68.3% harboring *parC* mutations and 27% harboring *gyrA* mutations. Given the unavailability of resistance testing for MRMs and the high prevalence of strains harboring MRMs (89.6%), sitafloxacin is the preferred treatment for *M genitalium* infections at our facility. Ando et al [20] reported that sitafloxacin monotherapy cleared strains harboring wild-type *parC* and *gyrA*. In addition to resistant strains, sitafloxacin demonstrated high effectiveness (92.9%) in clearing strains harboring *parC* G248T (S83I) mutations and wild-type *gyrA*, with 41.7% of those harboring *parC* G248T (S83I) and *gyrA* mutations. In contrast, moxifloxacin-based therapy cleared 96.5% of the strains harboring wild-type *parC* and *gyrA* [19]. The regimens mainly comprised sequential therapy with doxycycline followed by moxifloxacin and combination therapy with doxycycline and moxifloxacin. However, for strains harboring *parC* G248T (S83I) mutations and wild-type *gyrA*, the effectiveness of moxifloxacin-based therapy was limited to 54.2%. For those harboring *parC* G248T (S83I) and *gyrA* mutations, the effectiveness was further reduced to 18.8% [19]. Both sitafloxacin and moxifloxacin are newer-generation quinolones that exhibit a comparable incidence of gastrointestinal side effects [22,23]. These agents are less frequently associated with tendon rupture than levofloxacin, a prevalent fluoroquinolone drug [24]. Considering that both are broad-spectrum antibiotics, their impact on de novo resistance and the environment remains unclear and requires vigilant monitoring. A 7-day course of doxycycline is generally used to treat sexually transmitted infections with mild side effects, such as gastrointestinal disturbances [25].

Accordingly, we propose to conduct a multicenter, open-label randomized controlled trial aimed at comparing the efficacy and safety profiles of sitafloxacin and standard moxifloxacin-based sequential treatments in managing highly resistant *M genitalium* infections.

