### Randomization and Blinding

We will use a computer-based stratified randomization approach to ensure an equitable allocation of participants across different treatment groups, stratifying based on 2 factors: the facility where the study participants are enrolled and the anatomical site of *M genitalium* infection (categorized as the urethra, rectum, or a combination of both). Participants will be randomly assigned to groups at a 1:1 ratio. Blinding will not be implemented, as treatment success will be determined using the NAAT, an objective test. After randomization, patients will receive their respective treatments and will be scheduled for a follow-up test of cure 3 weeks after completing the regimen, with a permissible range of 10-100 days. The test-of-cure content of the positive sites will be assessed using the NAAT. When treatment fails, the number of short tandem repeats in the protein MG309 will be analyzed to differentiate a new infection from a persistent one, as previously reported [26].

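### The only stated genotype split is G248T yes/no, which pools gyrA wild-type and gyrA-mutant carriers whose success rates the article itself puts far apart

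*Protocol article*

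**What the plan says.** Under Efficacy Outcome, the genotype breakdown of the primary outcome is by one mutation: "For the primary outcome in the FAS, with or without the G248T (S83I) mutation, rates and their 95% CIs will be computed". Arms are compared with a chi-square test, and the analysis is repeated for G248T carriers in the per-protocol set. Randomization and Blinding stratifies by facility and infection site only.

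The Introduction treats gyrA as a second major determinant. It says that combined *parC* and *gyrA* "mutations limit the efficacy of fluoroquinolone-based therapy more significantly than single mutations". Among G248T carriers it gives sitafloxacin success of 92.9% with wild-type gyrA and 41.7% with mutant gyrA. For moxifloxacin-based therapy it gives 54.2% with wild-type gyrA, and for double mutants "the effectiveness was further reduced to 18.8" percent. The section closes by speaking of "treatments in managing highly resistant" infections.

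The sample size under Statistical Analysis rests on G248T strains as one group: "the success rates of sitafloxacin and moxifloxacin were anticipated to be 80% and 42%, respectively".

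**The concern.** The plan chooses a genotype split for its primary outcome, and that split leaves together two groups of carriers that, on the article's figures, differ by 51.2 points under sitafloxacin (92.9 - 41.7) and 35.4 points under moxifloxacin (54.2 - 18.8).

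Two things are at stake. The first is interpretation. A pooled sitafloxacin rate near 80% among carriers could be carried over to double mutants, for whom the article's own figure implies failure in 58.3% (100 - 41.7). Summary and Conclusions both look ahead to an influence on practice for resistant strains. The second is precision. gyrA status is strongly prognostic in both arms, so leaving it out of the carrier comparison lets chance imbalance in gyrA add variance that a stratified estimate would remove.

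**Working it through.** **Inputs.** The four stratum rates come from the Introduction. The pooled carrier rates of 78.9% (sitafloxacin) and 41.2% (moxifloxacin), the planning rates of 80% and 42%, two-sided 5% significance, 80% power, 50 per group and 10% dropout come from Statistical Analysis. Allocation is 1:1. Write g for the share of G248T carriers with mutant gyrA; the article does not state it.

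**The plan's own figure.** For 80% v 42%, the usual two-proportion formula gives [1.960 × √(2 × 0.61 × 0.39) + 0.842 × √(0.80 × 0.20 + 0.42 × 0.58)]² / 0.38² = 24.7, so 25 carriers per arm. Allowing for the 10-point superiority margin gives 41. The step from either figure to 50 uses a G248T prevalence that is not given (25/0.50 and 41/0.82 both give 50), so it cannot be checked. The dropout step reproduces: 50/0.9 = 55.6, so 56 per arm and 112 in total. The number of carriers per arm is therefore an assumption here, taken as 25, 34 (50 × 68.3%, where 68.3% is any parC mutation, so this is generous for G248T) or 50.

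**Implied gyrA share.**
- Sitafloxacin: (92.9 - 78.9)/(92.9 - 41.7) = 14.0/51.2 = 27.3%.
- Moxifloxacin: (54.2 - 41.2)/(54.2 - 18.8) = 13.0/35.4 = 36.7%.
- Upper assumption: 27/68.3 = 39.5%, if every gyrA mutant in the Japanese prevalence figures also carries a parC mutation.

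The rates come from different sources, so these shares are indicative only.

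**Pooled carrier rates**, (1 - g) × wild-type rate + g × mutant rate:

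| g | Sitafloxacin | Moxifloxacin | Difference (points) |
|---|---|---|---|
| 0% | 92.9% | 54.2% | 38.7 |
| 27.3% | 78.9% | 44.5% | 34.4 |
| 36.7% | 74.1% | 41.2% | 32.9 |
| 39.5% | 72.7% | 40.2% | 32.5 |
| 100% | 41.7% | 18.8% | 22.9 |

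Over the implied range the arm rates move by 4.8 and 3.3 points, but the difference by only 1.5.

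**Variance given up.** Per carrier per arm at g = 27%:
- Crude: 0.791 × 0.209 + 0.446 × 0.554 = 0.4126.
- Within gyrA strata: 0.73 × (0.929 × 0.071 + 0.542 × 0.458) + 0.27 × (0.417 × 0.583 + 0.188 × 0.812) = 0.3362.
- Term for the unequal effects in the two strata: ½ × 0.27 × 0.73 × (0.387 - 0.229)² = 0.0025.
- Ratio: (0.3362 + 0.0025)/0.4126 = 0.82, the large-sample limit.

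Simulation of the crude and Mantel-Haenszel risk differences (400,000 trials per setting) gives variance ratios at 25 and 50 carriers per arm of 0.838 and 0.830 at g = 27%, and 0.814 and 0.806 at g = 37%. The reduction is thus 16% to 19%. At g = 40% it is at most just under 20%. In standard error this is 8% to 10% (1 - √0.838 and 1 - √0.806).

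**Size of the double-mutant row.** 25 × 27.3% = 6.8 per arm; 34.15 × 27.3% = 9.3; 50 × 39.5% = 19.8. The 95% CI half-width for the arm difference is 1.96 × √[(0.417 × 0.583 + 0.188 × 0.812)/n], which is 47, 40 and 28 points respectively. Detecting 41.7% v 18.8% with 80% power would need 62 per arm with no margin. The row can only describe.

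**The case against.** The strongest reply is that the article says nothing false about gyrA, and that further subgroup tables and covariate adjustment may sit in the full protocol or analysis plan, which are not shown. That limits the point: it concerns the split and test that the article does choose, set against the article's own figures, and it would lapse if the full documents already separate gyrA.

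Several stronger readings are tempting and are not supported:

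- *The pooled comparison is biased.* It is not. Allocation is random, so gyrA is balanced in expectation and the ordinary standard error already covers chance imbalance.
- *The between-arm result swings with the gyrA mix.* The fall from 38.7 to 22.9 points needs shares of 0% and 100%. Over the implied shares the change is 1.5 points, and sitafloxacin leads in both strata.
- *Serious gyrA imbalance is likely.* With 25 carriers per arm, a gap of 12 points or more arises in 42% to 46% of trials (gyrA share 27% to 35%), but 12 points is then exactly three patients. With 34 or 50 carriers the figure is 22% to 25%.
- *The trial is confined to highly resistant infections and conceals the worst group.* Eligibility is any NAAT-positive adult, the Abstract states the objective for infections in general, and Limitations names strains with both mutations as a remaining difficulty. It does not, however, commit to a separate result for them.
- *The change costs nothing.* Efficacy Outcome ties the posttreatment-mutation estimate to participants still positive at test of cure, and nowhere is gyrA said to be read at baseline in everyone.

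What survives is the gap in interpretation and the loss of precision.

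**Conclusion.** The concern holds as a matter of reporting and efficiency, not of validity. The stated analysis will not show how either regimen performs in G248T carriers with mutant gyrA, and each arm's pooled carrier rate can be understood only with the gyrA mix beside it. The unstratified carrier comparison forgoes a variance reduction of about 16% to 19%, equal to roughly 19% to 24% more carriers (1/0.838 and 1/0.806). This rests on the article's four stratum rates holding in the trial, a gyrA share of 27% to 37% and 25 to 50 carriers per arm. It is worth settling before the data of this open-label trial are examined, because a gyrA split chosen afterwards would be post hoc.

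**What to change.** Under Efficacy Outcome:

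1. Prespecify descriptive success rates with 95% CIs in each arm for three pretreatment groups: no G248T, G248T with wild-type gyrA, and G248T with mutant gyrA.
2. Among G248T carriers, add a Mantel-Haenszel risk difference with 95% CI stratified by pretreatment gyrA status, using results where available and stating how many carriers lack one.
3. Do not extend a pooled G248T result to double mutants without showing that row, and label the row descriptive.

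The cost is mainly wording. The double-mutant row will hold perhaps 7 to 20 participants per arm, with wide intervals. If gyrA is not already read at baseline, sequencing the pretreatment samples of cured participants adds some laboratory work; reading it only in failures would not give success rates by gyrA.

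### The full-analysis-set primary test is a crude chi-square that leaves out pretreatment G248T status; it is valid but gives up roughly 4 to 10 points of power

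*Protocol article*

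**What the plan says.** Efficacy Outcome fixes the between-arm test for treatment success: "The chi-square test will be used to assess the statistical significance of treatment success between groups". Statistical Analysis makes the FAS the primary efficacy population. No adjustment is stated.

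Genotype appears elsewhere in the plan:

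- Efficacy Outcome plans FAS success rates with 95% CIs by presence or absence of G248T, and repeats the primary analysis among G248T carriers in the per-protocol set.
- A secondary outcome is "the emergence of posttreatment nucleotide polymorphisms in mutant strains compared with those in pretreatment samples".
- The sample size is framed around G248T: "the success rates of sitafloxacin and moxifloxacin were anticipated to be 80% and 42%, respectively", and "we aimed to enroll 50 participants per group (totaling 100 cases), considering the prevalence of the G248T mutation".
- Randomization and Blinding describes "stratifying based on 2 factors: the facility where the study participants are enrolled and the anatomical site". Genotype is not a stratification factor.

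The Introduction gives moxifloxacin-based clearance of 96.5% for wild-type strains and 54.2% for G248T with wild-type gyrA, and then: "For those harboring *parC* G248T (S83I) and *gyrA* mutations, the effectiveness was further reduced to 18.8" (per cent). For sitafloxacin it says that wild-type strains were cleared (no percentage), and gives 92.9% and 41.7% for the other two groups.

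**The concern.** By the article's own figures, pretreatment genotype predicts cure very strongly. Neither the randomisation nor the stated test uses it in the all-participant comparison. Reporting success rates by G248T status does not adjust the overall comparison, and the analysis of G248T carriers answers a different question in a different population.

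The stake is precision in a small trial. Variation in cure between genotypes stays in the error of the crude difference, although a baseline value that the trial needs anyway could remove part of it. A result near the threshold would also invite the remark that one arm happened to draw more resistant strains, and the primary analysis would have no direct answer.

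**Working it through.** **The plan's own figure.** The plan states "With a 5% significance level (2-sided) and 80% statistical power". Two proportions of 80% and 42% need 25 per arm against zero difference (30 with continuity correction). The stated 50 can be reached approximately in more than one way: 25 divided by an unstated prevalence of 50% gives 50, and a test against the 10-point margin gives 41 to 52 depending on the variance formula. The article does not say which route was used. The inflation reproduces: 50/0.9 = 55.6, so 56 per arm and 112 in total ("an expected dropout rate of approximately 10% was factored in, leading to a calculated sample size of 112 participants"). The check below uses 50 evaluable per arm.

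**Inputs and assumptions.** The Introduction gives parC mutations in 68.3% and gyrA mutations in 27%. Assumed: every parC mutation is G248T, every gyrA mutation sits on a parC mutation, and sitafloxacin cures 100% of wild-type strains. This gives shares of 31.7% wild-type, 41.3% G248T alone and 27% double mutant. Collapsed to G248T yes/no, success in carriers is:

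- sitafloxacin (0.413×0.929 + 0.27×0.417)/0.683 = 0.727
- moxifloxacin (0.413×0.542 + 0.27×0.188)/0.683 = 0.402

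**Formulas** (n per arm, genotype shares w, difference d overall and d_k within level k). Power = Φ[(d − 1.96·s0)/s1].

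- Crude: s0² = 2p̄(1−p̄)/n; s1² = [pS(1−pS) + pM(1−pM)]/n.
- Stratified: s0² = Σw·2p̄_k(1−p̄_k)/n; s1² = Σw[pSk(1−pSk) + pMk(1−pMk)]/n + Σw(d_k−d)²/(2n).

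**Case A, the Introduction's mix.** Overall success is 0.317×1 + 0.683×0.727 = 0.813 v 0.317×0.965 + 0.683×0.402 = 0.581, so d = 0.233.

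- Crude: s0 = 0.0919, s1 = 0.0889, power 72.3%.
- Stratified by G248T: s0 = 0.0833, s1 = 0.0800, power 80.8%.
- Simulation (40,000 trials): 72.5% and 81.0%, a gain of 8.5 points.

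**Case B, the plan's 80% v 42% in carriers, prevalence assumed 68.3%.** Overall 0.863 v 0.593, d = 0.271.

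- Crude: s0 = 0.0890, s1 = 0.0848, power 87.2%.
- Stratified: s0 = 0.0820, s1 = 0.0774, power 92.2%.
- Simulation: 88.4% and 92.8%, a gain of 4.4 points.

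**Case C, as B at an assumed 50% prevalence.** Overall 0.900 v 0.6925, d = 0.2075.

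- Crude: s0 = 0.0806, s1 = 0.0778, power 73.8%.
- Stratified: s0 = 0.0714, s1 = 0.0683, power 83.8%.
- Simulation: 75.7% and 84.6%, a gain of 8.9 points.

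**A mix matched to Statistical Analysis.** Case A implies 72.7% sitafloxacin success in carriers, but Statistical Analysis gives 78.9%. Solving 0.929 − x(0.929 − 0.417) = 0.789 gives x = 0.273, so the double-mutant share is 0.273×0.683 = 18.7%. With 31.7/49.6/18.7%, crude power is 81.7%, and 86.8% when stratified by G248T, a gain of about 5 points.

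**Against the 10-point margin** (simulated, G248T only): 52.7% to 59.0% in case B, 28.4% to 32.7% in case C, and about no gain near 40% prevalence.

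**Validity.** With moxifloxacin rates in both arms, simulated type I error is 5.3% for the crude test and 4.9% for CMH on G248T. The between-arm difference in G248T carriage has a chance SD of √(2×0.683×0.317/50) = 0.093.

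**If gyrA were also available.** Three-level CMH power is 89.1% in case A (gain 16.6 points) and about 93% in the matched mix (gain 11 to 12 points). Most scenarios give a total gain of 9 to 17 points.

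**Continuity correction.** In case B the continuity-corrected CMH test has 88.4% power, the same as the crude chi-square. The gains above are for the uncorrected test.

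**The case against.** The chi-square is a standard, valid test. Genotype imbalance under randomisation is random variation that the test and its interval already count. The article does not disregard G248T, since it plans rates by status and an analysis of carriers. It is a condensed article, and a statistical analysis plan may specify adjustment. All of this stands, and it makes the point one of efficiency and not of error. It does not remove the point, because the article names the unadjusted test as its method and reporting by subgroup does not sharpen the overall comparison.

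A reader might infer more, in three ways that the document does not support.

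- *That the crude test costs about 16 points of power.* That is near the top of the range. It needs three genotype levels, a mix that sits badly with the 78.9% in Statistical Analysis, and a test against zero difference.
- *That the full parC/gyrA genotype is already in hand.* Only G248T is named as an analysis variable. Baseline gyrA typing in everyone is never stated, and Table 1 lists no genotyping. Posttreatment resistance is to be estimated from positive test-of-cure results, so pretreatment gyrA sequencing might be confined to treatment failures. An undetermined level would then collect cured patients and could bias the adjusted estimate where the crude one is unbiased.
- *That chance imbalance makes the crude estimate biased.* It does not.

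**Conclusion.** The point holds as an inefficiency in a stated method. The FAS primary comparison leaves out a strong baseline predictor, G248T status, that the trial needs anyway for its planned FAS rates. At 50 per arm, using it would add about 4 to 10 points of power against zero difference, and less against the 10% margin.

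These sizes rest on the cure rates in the article, on G248T prevalences that it does not give for this trial (68.3% is its figure for all parC mutations; 50% and 40% are assumed), and on wild-type sitafloxacin cure at or near 100%. The direction of the gain against zero difference held in every uncorrected scenario run; its size did not stay constant. The larger gain from adding gyrA is conditional on typing that the article does not promise.

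**What to change.** In Efficacy Outcome, define the FAS primary comparison as a Mantel-Haenszel (or standardised) risk difference with 95% CI and a CMH test, stratified by pretreatment G248T status: present, absent or undetermined. State that:

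- classification uses the pretreatment sample only and is made without knowledge of outcome;
- the CMH test is used without continuity correction;
- the crude chi-square is kept as a supporting analysis.

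Add a gyrA level only if pretreatment gyrA is typed in all participants regardless of outcome, and say so explicitly. If the analysis plan already specifies adjustment, align the two documents before outcomes are examined by arm.

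For G248T this costs wording only, since the planned FAS rates already require the result. The small downside is sparse or undetermined levels, which limit how many factors can be stratified together; a standardised logistic model eases this. Universal gyrA typing, if not already planned, would be additional laboratory work.
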